## Abstract

**Background::**

Thyroid eye disease of orbital disease first, it is main and clinical expression with exophthalmos, visual impairment, serious influence patient's quality of life and beautiful, especially for the non-active Graves’ ophthalmopathy, there is no effective treatment methods at home and abroad, for the non-active thyroid eye disease only recommended surgery, but the procedure pain, poor curative effect, postoperative recurrence, most patients are difficult to accept. Pingmu Decoction can effectively reduce the degree of exophthalmus and TCM syndrome integral, and The combination therapy with acupuncture and moxibustion on the basis of Pingmu Decoction has achieved remarkable clinical effect, but the lack of rigorous evidence of evidence-based medicine (ebm). The test is designed to further evaluate flat mesh in active soup combined with acupuncture treatment of thyroid related ophthalmopathy card belongs to the yang qi-deficiency, phlegm and blood stasis block syndrome in patients with clinical efficacy and safety.

**Methods/Design::**

A prospective, randomized controlled clinical trial will be conducted to evaluate the efficacy and safety of Pingmu Decoction combined with acupuncture in the treatment of non-active thyroid-related eye disease in patients with Yang qi deficiency and phlegm-blood stasis syndrome. A total of 120 patients with non-active thyroid-related eye disease, namely deficiency of Yang qi and blockage of phlegm and blood stasis, are randomly divided into 3 groups and treated for 12 weeks. All three groups will maintain basic western medicine treatment. The primary outcomes are to observe the degree of prominence of eyes, and the TCM syndrome scores. The secondary result is clinical efficacy. Free triiodothyronine (FT3), free thyroxine (FT4), thyroid stimulating hormone (TSH), and thyroid stimulating hormone receptor antibody (TRAb)will be used as the observation indicators in this study. In addition, adverse reactions will be observed and recorded as safety indicators.

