### Study design

2.1

This is a prospective, randomized controlled clinical trial with three parallel arms. We will recruit 120 patients from The Longhua Hospital affiliated to Shanghai University of Chinese Medicine. All patients will be randomly assigned to the experimental group (Pingmu Decoction + acupuncture), control group 1 (Chinese medicine group) and control group 2 (acupuncture group). All patients will maintain basic treatment for thyroid-related eye disease: methimazole and levothyroxine sodium tablets (both from Merck & Co, LTD, Germany). Dosage will be adjusted every 28 days according to the patient's thyroid function level. Control group 1 (Chinese medicine group), Pingmu Decoction will be required to take orally twice a day, 1 bag each time., control group 2 (acupuncture group) will be treated with acupuncture alone. The experimental group was treated with pingmu Decoction combined with acupuncture. All treatments will be administered for 12 weeks.

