#### Interventions

2.5.4

All patients will maintain the basic treatment: methimazole and levothyroxine sodium tablets (both from Merck & Co, LTD, Germany). Dosage will be adjusted every 28 days according to the patient's thyroid function level.

Experimental group: Pingmu Decoction combined with acupuncture treatment.(Acupuncture points: Shangtianzhu, Fengchi, Sanyinjiao, Hegu, Waiguan and Yangbai are the main points, together with Cuanzhu on the head and face, Yuyao acupoints, Sizhukong acupoints, Toulinqi acupoints, Qiuhou acupoints, Qingming acupoints, Fengchi acupoints and opticoels. The index finger will be taken dajian acupoints, xiaojian acupoints wood acupoints;the pinkies will be taken Yanhuang acupoints, Huoxi acupoints;the legs will be taken Yichong acupoints. Erchong acupoints and Sanchong acupoints. Calvaria will select Baihui acupoint. All acupoints will be pierced vertically except Cuanzhu. Yuyao and Sizhukong acupoints. Frequency of acupuncture treatment: 45 minutes of needle retention twice a week). Control group 1: (Pingmu Decoction group): Patients will be given Pingmu decoction orally, 2 times a day, 1 bag each time. Control group 2 (acupuncture group): The patients will be treated only with acupuncture(acupuncture and moxibustion locations are the same as those of the experimental group). The course of treatment will be 12 weeks.

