### Safety assessments

2.8

Pingmu Decoction has been widely used in clinical practice, and has been found to be safe in clinical trials. Patients will be closely monitored for adverse reactions during this trial. In addition, laboratory tests will be performed at the beginning and end of the trial, including blood, urine, fecal, kidney, and liver function tests. If adverse events are reported, we will provide appropriate treatment to participants immediately.

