### Data collection and monitoring

2.10

Pre-clinical research training: All personnel in clinical research will be relatively fixed and receive unified training before the start of clinical trial, so that all researchers have a better understanding of the clinical trial plan.Data collection: Two inspectors will be appointed to oversee and inspect the research process. The data will be collected by the designated person. To ensure the accuracy of the data, two investigators will enter and proofread the data respectively. All cases will be completed in accordance with the design requirements of the Case Record Form. Withdrawal from the study and loss of follow-up (and the causes) will be fully documented.Quality control: The project leader supervises and checks the progress of the research, and checks whether the records and reports of the research data are true, accurate and complete. And the completed “Research Cases” for timely monitoring. All acupuncture and moxibustion operations will be carried out by specialized chief physicians to ensure the accuracy of acupuncture and moxibustion sites.

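### The clinical safety indicator is worded as adverse reactions; the text should say that all adverse events are recorded in every arm, whatever their judged cause

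*Protocol article*

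**What the plan says.** Two sentences in the protocol article say what clinical safety information is gathered. The abstract (Methods/Design) states that "adverse reactions will be observed and recorded as safety indicators". Section 2.8 (Safety assessments) states: "Patients will be closely monitored for adverse reactions during this trial".

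The other term, adverse events, appears in two places. Section 2.8 says: "If adverse events are reported, we will provide appropriate treatment to participants immediately". Section 2.5.3 (Termination and withdrawal criteria) lists adverse events among the reasons for stopping the experimental drug. Neither place makes adverse events the thing to be recorded or reported.

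Two further sources bear on safety. Section 2.8 plans that "laboratory tests will be performed at the beginning and end of the trial, including blood, urine, fecal, kidney, and liver function tests". Section 2.10 says: "Withdrawal from the study and loss of follow-up (and the causes) will be fully documented", and section 2.5.3 includes continuing deterioration among the withdrawal criteria.

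On the arms, section 2.1 says: "The experimental group was treated with pingmu Decoction combined with acupuncture". Control group 1 receives the decoction (section 2.5.4: "Patients will be given Pingmu decoction orally, 2 times a day, 1 bag each time"), and "control group 2 (acupuncture group) will be treated with acupuncture alone" (section 2.1). All three arms also stay on methimazole and levothyroxine.

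**The concern.** In trial usage an adverse event is any untoward occurrence, and an adverse reaction is the subset judged to be caused by treatment. A rule to record reactions therefore places a judgement of cause between the event and the record. Here the patient and the acupuncturist can tell which treatment is being given, because nothing in the article describes a placebo decoction, sham needling or blinding. The judgement would then be made with knowledge of the arm.

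The trial sets out to evaluate safety as well as efficacy. If recording depends on attribution, a difference between arms in recorded reactions may partly reflect belief about cause, and the protection that randomisation gives to the comparison is weakened. An event assigned to the eye disease may not be recorded for safety at all. That matters because the article itself names visual impairment, optic nerve injury and risk of blindness as consequences of this disease. An event that was never recorded may not be recoverable when the results are written up.

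**Working it through.** No arithmetic applies. The document gives no adverse event or reaction rate and no safety figure to reproduce. The check is a reading of every place that touches safety.

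1. **What is monitored and recorded.** Abstract, Methods/Design: adverse reactions. Section 2.8, monitoring sentence: adverse reactions. These are the only two sentences that say what clinical safety information is gathered, and they agree.

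2. **Where adverse events appear.** Section 2.8, as a trigger for treating the participant. Section 2.5.3, as a reason for stopping the drug. In both, the consequence is an action; neither says that the event enters the safety data. Section 2.8 thus uses two terms without saying whether they mean the same thing.

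3. **Is attribution defined?** No. The article gives no definition of an adverse reaction, no causality scale and no assessor. A reader who takes the term in its usual sense has no rule for applying it evenly across arms.

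4. **Would attribution be made knowing the arm?** The article does not use the word open. It follows from the design: one arm takes a decoction, one is needled, one has both, and no masking is described.

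5. **Would the disease's own harms be caught elsewhere?** Partly.
 - Exophthalmos and the TCM syndrome score are primary outcomes (section 2.7.1), so worsening on those measures is seen.
 - The secondary outcome (section 2.7.2) takes in ocular symptoms and signs, but its lowest category is lack of significant improvement, which does not separate worsening from no change.
 - Visual function is not a listed outcome.
 - Deterioration that leads to withdrawal is documented with its cause (sections 2.5.3 and 2.10), but no sentence makes it part of the safety data.
 - Visual worsening that does not lead to withdrawal and is put down to the disease has no stated place.

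6. **What is not affected.** The blood, urine, fecal, kidney and liver tests at the start and end need no attribution.

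7. **Direction.** Two opposing influences can be read from the text. The combination arm has one more added treatment to which an event could be assigned. Section 2.8 also opens by describing the decoction as already found safe, which could discourage attributing events to it. The document does not allow one to be weighed against the other.

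**The case against.** The best defence is that the wording is loose and not a deliberate restriction. The English is visibly translated, the term is undefined, and section 2.8 passes from reactions to events within a few lines as if they were one thing. A condensed article may also leave definitions, causality recording and safety tables to the full protocol, the Case Record Form or the analysis plan. Much of this stands. Intent cannot be settled from the text, and a missing definition alone would be no finding. What remains is that the article does state what is recorded, uses the narrower term both times, and uses the broader term elsewhere without connecting them.

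Three stronger readings are tempting, and the document does not support them.

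- **The safety outcome as a whole is restricted to attributed events.** It is not: the laboratory tests are part of the safety assessment and need no attribution.
- **Harms of the disease drop out of the trial.** This goes too far. Exophthalmos and ocular signs are efficacy outcomes, and causes of withdrawal are documented. The gap is narrower: such harms can be missing from the safety data.
- **The combination arm will show a predictable spurious excess, because it has two added treatments to blame against one.** No passage limits attribution to the decoction and the needling; all arms also take methimazole and levothyroxine, to which a reaction could equally be assigned. Any calculated excess would rest on an assumed event risk, an assumed probability of blame, and a choice of which treatments to count. Section 2.11 also specifies no between-arm safety test that could be said to be biased by a given amount.

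**Conclusion.** The point holds as a defect of wording with a real consequence if it is followed literally. The only stated rule for recording clinical safety information names adverse reactions, while adverse events are mentioned but not made what is recorded. In a design with no masking described, recording would then depend on attribution made with knowledge of the arm, and events put down to the disease, visual worsening in particular, could be left out of the safety data.

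This rests on two assumptions: that staff would read adverse reactions in its ordinary sense, and that the absence of any described placebo, sham or blinding means that there is none. The size and direction of any bias cannot be derived from the document, so no figure is offered. Laboratory safety data are unaffected.

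**What to change.** In the abstract and in section 2.8, reconcile the two terms by stating that all adverse events are recorded in every arm regardless of judged cause, with the judgement of relation to treatment recorded as a separate item. Tabulate the events by randomised arm, together with withdrawals for deterioration or for an adverse event; section 2.10 already requires the causes of withdrawal to be documented. Events judged to be treatment reactions can still be shown as a subset.

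The cost is a wording change in two places and one table, with existing staff and the existing Case Record Form. The downside is that reported event rates will be higher and will include events unrelated to treatment. No dose, treatment or stopping rule changes. If the wording was only loose, the edit costs almost nothing; if it was meant literally, the change is needed before data are collected.

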**Discussion::**

The results of this trial will provide convincing evidence for the efficacy and safety of Pingmu Decoction combined with acupuncture in the treatment of patients with non-active thyroid-associated eye disease with deficiency of Yang qi and phlegm and blood stasis block, and it will expand the treatment options for patients with non-active thyroid-related eye disease.

**Trial registration::**

Clinical Trials.gov ID: ChiCTR2000039626. Registered on 3 November 2020.

## Introduction

1

Thyroid associated ophthalmopathy, also known as Graves’ ophthalmopathy (GO), is a specific autoimmune disease related to thyroid disease and involving the eye socket. Its incidence ranks the first among adult orbital diseases.^[1]^ Its pathogenesis is still unclear, and it is related to environmental, immunological and genetic factors.^[2]^ The active phase of the disease is characterized by lymphocyte infiltration, fibroblast activation and edema.^[3]^ In the non-active stage, the main clinical manifestations were orbital fibrosis, soft tissue inflammation, eye movement disorder caused by eyeball protrusion, eyelid retraction, and orbital fibroblast inflammation.^[4]^ For the treatment of thyroid-associated ophthalmopathy in the active stage, the guidelines recommend that hormone shock therapy, immunosuppressive agents, orbital radiation therapy and surgery are often used in the active stage, while targeted surgery is used to relieve ocular symptoms in the inactive stage.^[5]^

Non-active thyroid associated ophthalmopathy is a refractory disease, which seriously affects the quality of life of patients. Currently, treatment means for non-active thyroid-related eye diseases are limited, and the curative effect is poor. Therefore, a treatment method with accurate curative effect and easy to be accepted by patients is urgently needed. In recent years, it has been found that traditional medicine has unique advantages in the treatment of this disease, which can significantly reduce local inflammation, improve visual acuity and reduce the protrusion degree and the TCM syndrome score, prevent the recurrence of the disease, and reduce the adverse reactions of Western medicine. The Pingmu Decoction is a Chinese medicine consisting of Radix Astragali(Huangqi), Herba Epimedii(Yinyanghuo), Miltiorrhiza (Danshen), Sinapis Alba (Baijiezi), Oldenlandia Diffusa (Baihuasheshecao), Semen Plantaginis (Cheqianzi), etc. It has beneficial temperature Yang, dispel phlegm stasis effect, and can effectively reduce the eyeball protrusion and TCM syndrome score in patients with non-active thyroid-related eye disease, which is characterized by deficiency of Yang qi and blockage of phlegm and blood stasis.^[6]^ According to [name],^[7]^ Pingmu Decoction can inhibit the accumulation of post-ocular adipose tissue in GO mice by inhibiting the proliferation activity of preadipocytes, reducing the differentiation of preadipocytes into adipocytes, and promoting the apoptosis of mature adipocytes after differentiation.^[8]^ It has been found in long-term clinical practice that Pingmu Decoction combined with acupuncture has a good effect on this disease, but there is still a lack of evidence to prove it. Therefore, we designed this prospective, randomized controlled clinical trial to further evaluate the efficacy and safety of Pingmu Decoction combined with acupuncture in the treatment of non-active thyroid-related eye disease, and to provide a new treatment regimen for non-active thyroid-related eye disease.

## Materials and methods

2

### Study design

2.1

This is a prospective, randomized controlled clinical trial with three parallel arms. We will recruit 120 patients from The Longhua Hospital affiliated to Shanghai University of Chinese Medicine. All patients will be randomly assigned to the experimental group (Pingmu Decoction + acupuncture), control group 1 (Chinese medicine group) and control group 2 (acupuncture group). All patients will maintain basic treatment for thyroid-related eye disease: methimazole and levothyroxine sodium tablets (both from Merck & Co, LTD, Germany). Dosage will be adjusted every 28 days according to the patient's thyroid function level. Control group 1 (Chinese medicine group), Pingmu Decoction will be required to take orally twice a day, 1 bag each time., control group 2 (acupuncture group) will be treated with acupuncture alone. The experimental group was treated with pingmu Decoction combined with acupuncture. All treatments will be administered for 12 weeks.

### Ethical issues

2.2

The trial will be conducted in accordance with the Declaration of Helsinki and Ethical Guidelines for Clinical Research, and the trial protocol has been approved by the Research Ethical Committee of Longhua Hospital Affiliated with Shanghai University of Traditional Chinese Medicine, Shanghai, China, (approval number: 2019LCSY001).

All participiants will be informed of the protocol, the purpose of the trial, and the rights, obligations, and risks involved with participation in the trial. Only patients who fully understand and sign the informed consent form will participate in the trial. In addition, the personal information about potential and e nrolled subjects will not be shared or maintained if unnecessary.

### Study participants

2.3

We will recruit patients from the outpatient department of Longhua Hospital affiliated to Shanghai University of Chinese Medicine. The planned recruitment period is 12 months.

### Sample size calculation

2.4

In this study, it is stipulated that only when the anterior ophthalmic process is reduced by ≥1 mm can be promoted. Exophthalmus references standard deviation is 1.3 mm, preliminary tests showed that Chinese herbal medicine could reduce the protrusion degree by 1.9 ± 1.1 mm,^[9,10]^ so we chose to reduce degree of exophthalmus to calculate the sample size, according to the α = 0.05, β = 0.1, σi is overall standard deviation for each group, μi means the population mean of each group is 1.3, K refers to the number of sample groups are 3, μ = Σμi/k, ψ of value through the check ψ of table that is 2.52, the formula for sample size = ψ2(Σσi2/k)/[Σ(μi−μ)2/(k−1)] calculated sample size is equal to about 36, considering a 10% loss to follow-up, determine the test each sample size for 40 cases, The total sample size is 120.

### Criteria

2.5

#### Inclusion criteria

2.5.1

Participants will be included if they fulfill the following conditions:

Satisfy the diagnostic criteria of GO for Western medicine^[11]^ and traditional Chinese medicine, which the TCM types belong to yang-Qi deficiency and Phlegm-blood Stasis syndrome.^[12]^Aged 18 to 70 yearsWill be repulsing surgical treatmentA history of GO and normal serum thyroid hormone levels (FT3, FT4) for at least 2 monthsSign informed consent

#### Exclusion criteria

2.5.2

Patients with any of the following conditions will be excluded:

Failure to satisfy the inclusion criteriaOther reasons which caused the eyeball protrusion: such as protrusion of the eye caused by nearsightedness, Primary orbital tumor, Orbital inflammatory pseudotumor, eye metastasis and other diseasesThose with diseases of the liver, kidney, hematopoietic system, or hyperthyroidism crisis tendency and mental illnessThose who are participating in clinical studies of other drugsThose who are pregnant, nursing or preparing for pregnancy

#### Termination and withdrawal criteria

2.5.3

Important deviations occurred in the implementation of clinical research protocols, which made it difficult to evaluate drug effectsDuring the experiment, the condition of the patients continued to deteriorate and dangerous events are likely to occurSubjects experienced certain comorbidities, complications, or specific physiological changes during the study periodDiscontinuation of experimental drugs due to adverse events or other reasonsSubjects do not take the test drug as required and complete the follow-up as planned, are unwilling to continue the clinical trial

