### Randomization and allocation

2.6

We will randomize all included patients using a table of random numbers. The 120 patients will be randomly divided into the experimental group, control group 1 and control group 2 in a 1:1:1ratio according to the treatment order.

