#### Primary outcomes

2.7.1

Exophthalmos degree. Measurement of prominence of the eyeball: Use the ocular protrusion measuring instrument (model YZ9) to measure the degree of exophthalmia(Which brand is called Crane and produced by Suzhou liuliu Vision Co., LTD.)TCM syndrome integral

According to the diagnostic criteria of Deficiency of Yang qi and blockage of phlegm and blood stasis formulated in 2002 edition of Clinical Research Guidelines for New Chinese Medicine.^[11]^ Main symptoms: fear of cold, lack of power, eyeball swelling pain; Secondary symptoms: tepid limbs, pale face, self - perspiration. The body of the tongue is fat or normal, the tongue is pale purple, or there are petechial spots, or the veins under the tongue are purple and angry. The tongue coating white greasy, pulse heavy fine astringent. According to the degree of occurrence of the main symptoms: no, mild, moderate and severe, they will be recorded as 0, 2, 4 and 6 points respectively, and according to the degree of occurrence of secondary symptoms: no, mild, moderate and severe, they will be recorded as 0, 1, 2 and 3 points respectively. The tongue image and pulse image of the block syndrome of phlegm and blood stasis will be scored 1 and 0 points according to whether they are consistent with deficiency of Yang qi and blockage of phlegm and blood stasis. TCM syndrome integrals will be recorded once before and after treatment in the three groups.

Efficacy of TCM symptoms will be determined by integral method: Efficacy index(n) = ((post-treatment score − pre-treatment score)/(pre-treatment score)) × 100%

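### Section 2.5.3 does not separate stopping treatment from leaving the study, which leaves the comparison open to bias from outcome-related withdrawal that differs by arm

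*Protocol article*

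**What the plan says.** All references are to the protocol article.

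- **Section 2.5.3 (Termination and withdrawal criteria)** is a single list. It covers important deviations that make the drug effect hard to judge, patients in whom "the condition of the patients continued to deteriorate and dangerous events are likely to" occur, comorbidities or complications, stopping the experimental drug for adverse events or any other reason, and subjects who "do not take the test drug as required and complete the follow-up as planned, are unwilling to continue the clinical trial". It does not distinguish ending treatment from ending participation.
- **Section 2.10 (Data collection and monitoring)** says: "Withdrawal from the study and loss of follow-up (and the causes) will be fully documented". It says nothing on whether these patients are measured again.
- **Section 2.7.1 (Primary outcomes)** names exophthalmos and the TCM syndrome score. For the score: "TCM syndrome integrals will be recorded once before and after treatment in the three groups". For exophthalmos it gives the instrument ("Use the ocular protrusion measuring instrument (model YZ9) to measure the degree of exophthalmia") but no visit times.
- **Section 2.1 (Study design)** says "All treatments will be administered for 12 weeks", so the after-treatment record falls at week 12. It also says that "control group 2 (acupuncture group) will be treated with acupuncture alone". Section 2.5.5 identifies the trial drug as Pingmu Decoction.
- **Section 2.6 (Randomization and allocation)**: patients are "randomly divided into the experimental group, control group 1 and control group 2 in a 1:1:1ratio".
- **Section 2.4 (Sample size calculation)** allows for 10% loss to follow-up, from about 36 to 40 per arm and 120 in total.

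**The concern.** Every reason in the list arises after randomisation, and several are tied to how the patient is doing. If meeting one of them ends participation, and the final measurement is not taken, the patients with an outcome are a selected group. For the TCM score there is no intermediate value to fall back on.

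The selection also need not be the same in each arm. Stopping the experimental drug and not taking the test drug are worded for the decoction only. Read literally, neither can be met by a patient in control group 2. Burden differs as well: the decoction twice daily, needling twice weekly for 45 minutes, or both (section 2.5.4).

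What is at stake is whether the arms are still comparable at week 12. A later analysis plan can choose an analysis set and a missing-data method, but it cannot recover a measurement that was never taken.

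**Working it through.** **1. The plan's own loss allowance.** 36 / (1 − 0.10) = 40 per arm and 3 × 40 = 120, which reproduces. Ten per cent of 120 is 12 patients, leaving 108. The 36 itself cannot be reproduced: section 2.4 gives one value, 1.3, for the mean of every group, so the between-group term in its formula is zero. That is a separate matter, and nothing below uses the 36.

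**2. What the text settles and leaves open.**

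| Question | Text |
|---|---|
| Is stopping the drug a withdrawal criterion? | Yes (2.5.3) |
| Is it separated from leaving the study? | No (2.5.3) |
| Are withdrawn patients measured at week 12? | Neither provided for nor ruled out (2.5.3, 2.10) |
| Single post-treatment record? | Stated for the TCM score; no timing stated for exophthalmos (2.7.1) |
| Do all triggers apply in all arms? | Not literally; two name only the drug (2.5.3 with 2.1 and 2.5.5) |

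**3. Possible size for exophthalmos.** Inputs: SD 1.3 mm (section 2.4). Loss rates, and the correlation ρ between the tendency to withdraw and the outcome, are assumptions, because the document gives neither. No true difference between arms is assumed.

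If the fraction q of an arm most prone to withdraw is lost, the mean reduction among those who remain rises, for a normal outcome, by

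shift = ρ × SD × φ(z_q) / (1 − q).

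At ρ = 1, where exactly the worst outcomes are lost:

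| q | Shift, SD 1.3 mm | Shift, SD 1.1 mm |
|---|---|---|
| 5% | 0.141 | 0.119 |
| 10% | 0.253 | 0.214 |
| 15% | 0.357 | 0.302 |
| 20% | 0.455 | 0.385 |

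The SD of 1.1 mm is the one that section 2.4 attaches to the preliminary 1.9 mm reduction.

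Take 20% loss in one arm and 5% in each of the others: 8 + 2 + 2 = 12 of 120, the plan's own 10% overall, unevenly spread. The false difference between the 20% arm and a 5% arm is:

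- ρ = 1: 0.455 − 0.141 = 0.314 mm by formula, 0.318 mm by simulation (40 per arm, 4,000 runs). With SD 1.1 mm: 0.385 − 0.119 = 0.266 mm.
- ρ = 0.5: 0.5 × 0.314 = 0.157 mm by formula, 0.154 mm by simulation.
- ρ = 0: about 0 (simulated 0.002 mm).

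With equal 10% losses in all arms the simulated difference is within 0.01 mm of zero at every ρ tried.

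**4. Scale.** With 32 and 38 patients left, the standard error of a difference is 1.3 × √(1/32 + 1/38) = 0.31 mm. A false difference of 0.15 to 0.32 mm is thus about half to one standard error, and 15% to 32% of the 1 mm reduction that section 2.4 sets as its threshold. In the same simulation the false-positive rate of the three-group ANOVA at the 5% level was about 0.25 at ρ = 1, 0.08 at ρ = 0.5 and 0.05 at ρ = 0.

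**5. TCM score.** No SD is given, so only SD units are possible: 0.314 / 1.3 = 0.24 SD at ρ = 1 and 0.12 SD at ρ = 0.5, if the score is roughly normal.

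**The case against.** The strongest reply is that this reads silence as a rule. The article is condensed, its flow figure is not shown, and no sentence says that assessment stops or that data are discarded. Full documentation of withdrawals is compatible with a measurement at withdrawal or at week 12. Analysis sets and missing-data rules normally sit in an analysis plan.

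Much of this stands, and it limits the point. A reader might infer any of the following, and the document supports none of them:

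- **That the outcome is lost for withdrawn patients.** The text neither provides for nor excludes measuring them.
- **That exophthalmos has a single post-treatment measurement.** Only the TCM score has a stated schedule.
- **That any patient who worsens or deviates is removed.** The deterioration item also requires that dangerous events be likely, and the deviation item covers only important deviations that hinder evaluation.
- **That the comparison is biased.** That needs withdrawal both related to outcome and different between arms, and neither is established. Some who stop may have done well, so the direction is also open.
- **That patients without an outcome should be counted as treatment failures.** That is a debatable imputation, which can itself favour the arm with fewer losses, and it belongs to the analysis plan.

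What does not fall is the rule as written. Section 2.5.3 itself puts drug discontinuation under a withdrawal heading, section 2.10 speaks of withdrawal from the study, and two triggers name a drug that one arm never receives. Part of the last item describes people unwilling to continue; where they withdraw consent, no measurement can be required of them. That does not cover those who merely stop the drug or deviate.

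**Conclusion.** The point holds as a badly fixed rule that leaves the comparison open to bias, not as a demonstrated bias. Followed as written, section 2.5.3 can cost the final outcome for patients selected on grounds that arise after randomisation and may relate to outcome. The wording of two triggers lets that selection differ between the decoction arms and the acupuncture-only arm.

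The illustrated size is a false difference of about 0.15 mm (ρ = 0.5) to about 0.32 mm (ρ = 1) for 20% against 5% loss. It rests on assumed loss rates and correlations, an SD of 1.3 mm, a normal outcome, and no measurement of withdrawn patients. The upper end is an extreme, since it requires that exactly the worst outcomes be lost. With equal losses, or withdrawal unrelated to outcome, the expected difference is about zero. This is a cheap improvement that should be made while patients can still be measured.

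**What to change.** Leave the clinical reasons for stopping treatment as they are. Add to section 2.5.3, and align section 2.10 with it:

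1. Stopping treatment, or deviating from the protocol, is not withdrawal from the study. Only withdrawal of consent ends follow-up.
2. Exophthalmos and the TCM score are measured at week 12 in every randomised patient who has not withdrawn consent, whatever treatment was received.
3. These patients are analysed in the arm to which they were assigned.

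The sponsor should also reconcile the two drug-worded triggers with the existence of an acupuncture-only arm, so that the reader knows how they apply there.

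The cost is a few sentences and a week-12 visit for a few patients: about 4 per arm if the whole 10% allowance were patients who stop early and can still be seen. The effect estimate may be slightly smaller, because it then includes patients who did not complete treatment.
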